### Eligibility criteria

Medical dialogues in the development stage should comply with the following criteria: (1) Inclusion criteria: We will include dialogues from both initial consultations and follow-up visits that provide adequate medical history information while minimizing the inclusion of physical examination details. The diagnosis should correspond to diseases ranked within the top 5 outpatient cases for each subspecialty, based on data from the Eye & ENT Hospital of Fudan University over the past 3 years. (2) Exclusion criteria: we will exclude diseases that are diagnosed or triaged solely based on physical examinations.

Anterior segment images in the development stage should comply with the following criteria: (1) Inclusion criteria: Individuals should have a documented medical history and diagnosis; Following a review of the medical history, both the diagnosis and subspecialty triage should have been confirmed according to the reference standard, as specified below. (2) Exclusion criteria for anterior segment images: photos with insufficient lighting or facial covering.

In the silent evaluation and early clinical evaluation stages, all cases should adhere to the following criteria: (1) Inclusion criteria: informed consent must be obtained from all participants; participants should have specific concerns or issues directly related to their eyes; for patients who are unable to provide informed consent due to incapacity or are underage or otherwise vulnerable, consent from must be obtained from their legal guardians and legal guardians are required to assist in the collection of medical history and images; each participant's diagnosis and subspecialty triage must be validated using a reference standard as detailed below. (2) Exclusion criteria: cases where the diagnosis and triage results fail to generate due to a program error; patients who, in the opinion of the attending physician or clinical study staff, are too medically unstable to participate in the study safely; diseases with prevalence below the 5-percentile threshold are not included.

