### Reference standard

The reference standard is determined by an expert panel comprising five senior consultants (with a minimum of 5 years of clinical experience). A consensus of diagnosis and triage is required from at least three out of these five experts after a comprehensive review of the patients' medical histories. In cases where expert consensus cannot be achieved, patients will be asked to attend follow-up appointments, during which additional examinations may be recommended. If, after 3 months of follow-up, a definitive diagnosis remains elusive, the patient will be excluded from the study.

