### Outcome measure

The primary outcome is the correctness of the AI system's diagnosis, and the secondary outcome is the correctness of the AI system's triage decisions. The above assessment takes place by comparing the AI-generated results with the reference standards established by expert panels:

(1) Judged as correct: when the system's results are entirely consistent with the reference standard; when the system's results fall within the range of the reference standard.(2) Judged as incorrect: when there is no overlap between the system's results and the reference standard; when the system fails to provide any diagnostic or triage information.(3) In the following scenarios, additional discussion and assessment are required. A consensus is considered to be reached when at least 2 out of 3 experts are in agreement: when the reference standard includes the system's results; when there is partial overlap between the system's results and the reference standard.

In addition to assessing accuracy, we will also evaluate the quality, empathy, and patient satisfaction of the AI system's responses. Three independent evaluators (licensed healthcare professionals), who are blinded to the accuracy of the responses, will judge both “the quality of information provided” (very poor, poor, acceptable, good, or very good) and “the empathy of information provided” (not empathetic, slightly empathetic, moderately empathetic, empathetic, and very empathetic) on a scale of 1–5. Notably, these quality and empathy rating assessors evaluate the quality and empathy of the AI results based solely on the AI output, without knowledge of the patient's complete clinical information, reference standard results, or the correctness of the AI output.

During the early clinical evaluation stage, patient satisfaction (not satisfied, slightly satisfied, moderately satisfied, satisfied, and very satisfied) will be measured on a scale of 1–5 after AI responses have been generated. When evaluating satisfaction of the AI output, the patients are only aware of the AI output and remain uninformed about the reference standard results or the correctness of the AI output. After the evaluation, they can be informed of the reference standard results and the correctness of the AI output.

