### Statistical analysis

To assess the AI system's diagnostic and triage performance, we will use the one-vs.-rest strategy and calculate the area under the receiver-operating-characteristic curve (AUC), sensitivity, specificity, accuracy, positive predictive values and negative predictive values for disease diagnosis and subspecialty triage using IBM SPSS Statistics 26 software. Specifically, sensitivity measures the AI system's ability to correctly identify positive cases, such as diagnosing a specific disease or assigning a patient to the correct subspecialty. It is calculated by determining the ratio of true positives (correctly identified positive cases) to the sum of true positives and false negatives (missed positive cases). Conversely, specificity evaluates the AI system's capacity to accurately identify negative cases. For instance, it assesses the system's ability to correctly exclude the presence of a particular disease or to avoid assigning a patient to an incorrect subspecialty. Specificity is determined by calculating the ratio of true negatives (correctly identified negative cases) to the sum of true negatives and false positives (incorrectly identified negative cases). Accuracy, which indicates the proportion of correct classifications made by the AI system, will be determined as follows: Accuracy = (True positive + True negative)/(True positive + True negative + False positive + False negative). This parameter offers an overarching evaluation of the system's ability to make precise diagnoses and triage assignments. In addition to sensitivity, specificity, and accuracy, we will also calculate AUC, positive predictive values and negative predictive values. These parameters collectively provide a comprehensive assessment of the AI system's diagnostic and triage capabilities, ensuring a thorough evaluation of its performance. Subgroup analyses will be performed to explore the influence of lesion location (anterior segment disorders vs. posterior segment disorders) on the performance of the multimodal AI system. A *post-hoc* power calculation will also be conducted to assess how lesion locations influence the AI system's performance.

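### Runs that fail with a program error are excluded under Eligibility criteria, but cases with no output are scored incorrect under Outcome measure; following the exclusion inflates the proportion correct, sensitivity and NPV

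*Protocol article*

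**What the plan says.** Under Eligibility criteria, the exclusions for the silent and early clinical evaluation stages include "cases where the diagnosis and triage results fail to generate due to a program error".

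Under Outcome measure, the protocol states: "The primary outcome is the correctness of the AI system's diagnosis, and the secondary outcome is the correctness of the AI system's triage decisions". One of the two situations that make a result incorrect is "when the system fails to provide any diagnostic or triage information". This rule carries no restriction to a stage and no exception for technical faults.

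Under Statistical analysis, "we will use the one-vs.-rest strategy and calculate the area under the receiver-operating-characteristic curve (AUC), sensitivity, specificity, accuracy" and the predictive values are planned. Sensitivity is TP/(TP+FN). Specificity is TN/(TN+FP) and is described as "the system's ability to correctly exclude the presence of a particular disease or to avoid assigning a patient to an incorrect subspecialty". The section does not say how a case without output enters these tables.

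Under Hypotheses, the sensitivity marks for diagnosis are 85% in the silent evaluation and 75% in the early clinical evaluation, each with 95% specificity. PPV and NPV marks are set for triage: 85% and 95%, then 80% and 95%.

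**The concern.** The same event, a run that ends with nothing on the screen, is removed by one section and counted as a failure by another. Which section is followed changes the denominator of the primary outcome.

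The exclusion is written as an eligibility criterion, but nobody can know whether a patient meets it until the index test has been run. It therefore selects on the behaviour of the product being evaluated. The Discussion presents the study as a test of the reliability and feasibility of a smartphone system in real-world use, so failure to generate a result is part of what is being measured. If such failures are left out, a stage could be reported as reaching its sensitivity mark when, over all patients tested, it did not.

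**Working it through.** **Inputs.** From the protocol: marks of 85% and 75% for sensitivity, 95% for specificity, and 22 patients per disease in the silent evaluation. Assumed: the failure rate f, since the protocol gives none, and independence of failure from disease and case difficulty. A mark is taken as met when the point estimate reaches it.

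**The plan's own figure.** 22 × 4 diseases = 88, raised to 100. The multiplication is right. The 22 itself cannot be reproduced, because the null values are not stated. It lies among the results for plausible nulls (for example, sensitivity 0.85 against 0.55, two-sided, needs 21 by normal approximation and 23 exactly). Nothing below depends on how it was derived.

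**Step 1, no failure rate needed.** Take 22 patients with one disease: 18 correct, 3 wrong, 1 without output.
- Outcome measure rule: 18/22 = 81.8%, below 85%.
- Eligibility rule: 18/21 = 85.7%, above 85%.

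**Step 2, sensitivity in general.** All-case sensitivity = completed-run sensitivity × (1 − f), so exclusion multiplies it by 1/(1 − f).

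| Completed-run sensitivity | f = 2% | f = 5% | f = 10% |
|---|---|---|---|
| 0.85 | 0.833 | 0.8075 | 0.765 |
| 0.75 | 0.735 | 0.7125 | 0.675 |

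Near the 75% mark: 0.78 × 0.95 = 0.741 (missed), 0.80 × 0.95 = 0.760 (met), 0.80 × 0.90 = 0.720 (missed). To reach 85% with failures counted, completed runs need 0.85/(1 − f) = 0.867, 0.895 and 0.944 at f = 2%, 5% and 10%.

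The overall proportion correct changes by the same factor.

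**Step 3, the other one-vs.-rest measures.** Assume 100 patients, 25 with the index disease, sensitivity 0.85 and specificity 0.95 among completed runs, and f = 10%. There are then 90 completed runs (22.5 with the disease, 67.5 without): TP = 19.125, FN = 3.375, FP = 3.375, TN = 64.125. The failures are 2.5 with the disease and 7.5 without. No output is treated as no positive call.

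| Measure | Failures excluded | Failures included |
|---|---|---|
| Sensitivity | 19.125/22.5 = 0.850 | 19.125/25 = 0.765 |
| NPV | 64.125/67.5 = 0.950 | 71.625/77.5 = 0.924 |
| PPV | 19.125/22.5 = 0.850 | 19.125/22.5 = 0.850 |
| Specificity | 64.125/67.5 = 0.950 | 71.625/75 = 0.955 |
| Accuracy | 83.25/90 = 0.925 | 90.75/100 = 0.9075 |

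PPV does not move, because a case without output is never called positive. Specificity is slightly lower with exclusion, because an unaffected patient without output is a true negative.

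Accuracy with failures included is (1 − f) × completed-run accuracy + f × (1 − prevalence). Exclusion therefore lowers it when 1 − prevalence exceeds completed-run accuracy. With these inputs that means 1 − p > 0.85p + 0.95(1 − p), or p < 0.05/0.90 = 5.6%.

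**The case against.** The strongest reply is that the two rules can be read as compatible. The exclusion is tied to a program error, while the scoring rule could be meant for a run that completes but offers no answer. On that reading a software or network fault is excluded, an unhelpful answer is wrong, and each rule has its own work. The definition of a program error might also stand in a fuller protocol than this article.

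Part of this stands: the qualifier is there, and not every case without output is excluded. But the article does not draw that line, and its scoring rule covers failure to provide any information without regard to cause. Even if the line were drawn, the exclusion would still act after the index test and remove failures of the product itself.

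It is also fair that the failure rates are hypothetical. With 80% sensitivity and 5% failures, the 75% mark is still met. The one-failure example in 22 patients needs no rate, but it was chosen to sit at the mark.

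A reader might go further and infer three things that the documents do not support.

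- *That every accuracy figure is inflated.* The one-vs.-rest definitions do not give this. It would follow only if each failure were also a false positive for the diseases the patient does not have, and the protocol states no such scoring.
- *That the 90% sensitivity mark is affected.* It belongs to in silico development, where this exclusion does not apply.
- *That two other exclusions bias results the same way.* One applies if, after 3 months, "a definitive diagnosis remains elusive, the patient will be excluded from the study". The other states that "diseases with prevalence below the 5-percentile threshold are not included". Both are stated scope choices. The direction of the first depends on the system doing worse in unresolved patients, and these have no reference disease to enter in a table. The second removes true negatives as well as possible false positives. The protocol gives no figure that settles either.

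**Conclusion.** The concern holds in limited form. In the silent and early clinical evaluations, the exclusion and the scoring rule overlap for a run that yields nothing because of a fault, and the protocol does not say which prevails. Following the exclusion overstates the overall proportion correct, sensitivity and NPV. It does not inflate PPV or specificity when no output counts as no positive call, and it can shift per-disease accuracy up or down.

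The factor for sensitivity is 1/(1 − f), which assumes failures unrelated to disease and difficulty. At assumed rates of 2% to 10%, a completed-run sensitivity of 85% corresponds to 83.3% to 76.5% over all patients. The true size is unknown, because no failure rate is given. The point still needs correcting before analysis: at 22 patients per disease a single failure can reverse the finding on the 85% mark, so the choice between two written rules can decide a primary result.

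**What to change.** Delete the program-error exclusion from Eligibility criteria. In the primary analysis of both evaluation stages, apply the existing rule in Outcome measure, so that a case without output is incorrect. State under Statistical analysis how it enters each table: a false negative for the patient's reference disease and no positive call for the others, with the same convention for subspecialty triage. Report the number of failures by site and stage. Give the analysis of completed outputs as secondary.

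The cost is the removal of one exclusion, a sentence on how such cases are tabulated, and one extra analysis with the failure counts. The downside is slightly less favourable sensitivity and NPV.

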### Recruitment

For the *in silico* development stage, all cases will be recruited at the Eye & ENT Hospital of Fudan University. Specifically, researchers will record doctor-patient conversations at each subspecialty clinic. The conversations will undergo a curation process that involves the removal of filler words and irrelevant content, resulting in the creation of medical dialogues. Eligible medical dialogues will be continuously enrolled from June 1 to July 1, 2023. Regarding the anterior segment images, researchers will browse medical records and consistently gather images related to the top 1–5 diseases in each subspecialty from January 1, 2020 to July 1, 2023. The initial sample size consists of 20 dialogues per specialty and 50 images per disease, which is then adjusted according to the AI system's performance.

For the silent evaluation stage, data will be continuously gathered in Shanghai from July 10 to July 15, 2023, with a sample size of 100 cases. Two pre-trained researchers will serve as observers in outpatient clinics, ensuring they do not interfere with standard management procedures. Upon obtaining the patients' consent (as detailed in Supplementary material 2), the researchers will collect the patients' medical information and enter it into the system. For patients who are prescribed with anterior segment imaging test by outpatient clinic doctors, the researchers will collect the images from the electronic medical system.

For the early clinical evaluation stage, eligible participants will be continuously recruited at three distinct sites. The Shanghai site serves as an internal validation dataset, with data collection spanning from July 21 to August 20, 2023. The Nanjing and Suqian sites function as external validation dataset, with data collection scheduled from August 21 to August 31, 2023. Each center will be staffed with two pre-trained researchers. These researchers will be responsible for patient recruitment across various subspecialty clinics within their respective centers. Once patients provide their consent (as detailed in Supplementary material 4) to participate in the study, the researchers will gather medical history and acquire anterior segment images. Following this, outpatient physicians will proceed with clinical diagnosis and treatment.

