### Blinding

The blinding methods vary depending on the roles of the researchers and the stage of the study in which the researchers and subjects are involved. AI developers and AI output correctness assessors have access to complete patient information, including medical history, reference standard results, and AI output for determining correctness.

In our study, two roles are subject to blinding. (1) Reference standard assessors: These assessors possess knowledge of the patient's clinical information but are unaware of the AI output or its correctness. This approach helps mitigate information bias and classification bias. (2) Clinical researchers: These researchers are responsible for inputting data into the multimodal AI program. During the *in silico* development stage, they have access to all patient clinical information and reference standard results. However, during the silent evaluation and early clinical evaluation stages, they only have access to the patient's clinical information without knowledge of the reference standard. This approach helps mitigate diagnostic suspicion bias.

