## Discussion

Our study aims to develop a multimodal AI system based on ChatGPT-3.5 and explore its performance for the diagnosis and triage of ophthalmic diseases. Existing alternative proprietary LLMs include ChatGPT-4.0 and Google Bard (Lim et al., 2023). Additionally, there are some open source LLMs that can be locally deployed. As we plan to apply our designed multimodal AI system in clinical experiments, it necessitates swift interactive responses and the ability to handle parallel tasks. There are two primary reasons for not utilizing locally deployed LLM models. Firstly, their text generation performance is not as robust as ChatGPT, which hinders rapid interaction and concurrent conversations. Secondly, it demands a substantial amount of data for initial local training, which doesn't align with our objective of rapid product development and application in clinical experiments. ChatGPT currently stands out as the most proficient and reliable LLM product on the market for interactive applications. While ChatGPT-4.0 lacks support for prompt engineering, and Google Bard was not yet available at the outset of our research, we made the decision to develop our multimodal AI system based on ChatGPT-3.5.

One of the strengths of our multimodal AI system is its applicability to different ophthalmic diseases. Previous studies predominantly rely on photographs to detect certain ocular and visual abnormalities (Ting et al., 2019; Tan et al., 2021; Tiwari et al., 2022; Lou et al., 2023; Shao et al., 2023a). These image-centric technologies, while valuable, have limitations when it comes to large-scale applications across diverse ophthalmic conditions. The limitations primarily stem from the absence of comprehensive medical histories, which are crucial for accurate diagnosis (Ting et al., 2019; Moor et al., 2023). Therefore, we aim to integrate medical history inquiry with image-based diagnosis to empower a multimodal AI system. According to the protocol, we will evaluate the performance of this system in detecting most of the common ophthalmic diseases, including anterior and posterior segment disorders, strabismus, neoplasms, aesthetic abnormalities and ocular manifestations of systemic diseases. This system is efficient for triage procedures. During registration, pre-registration desk staff can assist patients with AI-powered diagnosis and triage, guiding them to subspecialty appointments.

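### Rare-disease and unresolved patients are excluded largely after the AI has been run, which can overstate specificity, PPV and overall accuracy in undiagnosed attenders

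*Protocol article*

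**What the plan says.** The Eligibility criteria section sets two conditions for the silent and early clinical evaluations that depend on the final diagnosis. As an inclusion criterion, "each participant's diagnosis and subspecialty triage must be validated using a reference standard as detailed below". As an exclusion, "diseases with prevalence below the 5-percentile threshold are not included". The text does not say in which population prevalence is measured, over what period, or when the threshold is fixed.

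The Reference standard section asks for agreement by at least three of five experts and sends cases without consensus to follow-up. It then adds: "If, after 3 months of follow-up, a definitive diagnosis remains elusive, the patient will be excluded from the study".

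Two sections bear on timing. For the early clinical stage, Recruitment has history and images collected first, and then: "Following this, outpatient physicians will proceed with clinical diagnosis and treatment". Blinding says of the staff who enter the AI data in both stages that "they only have access to the patient's clinical information without knowledge of the reference standard".

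On intended use, the Discussion says: "During registration, pre-registration desk staff can assist patients with AI-powered diagnosis and triage". It also narrows the evaluation to most of the common eye diseases. The Limitation section concedes that rare diseases may be missed, but gives small sample size as the reason and does not mention the exclusion.

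**The concern.** A patient at a registration desk has no final diagnosis, so nobody can sort that patient by disease rarity, or by whether experts will later agree. The evaluation does sort patients this way, largely after the AI inputs have been taken. If the AI gives a rare-disease patient a common-disease label, that is a false positive in the table for that label, and the exclusion deletes it. The reported specificity, PPV and share of correct patients then describe a filtered group.

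Specificity of at least 95% is part of the primary target in each stage, and PPV is a secondary target for triage (Hypotheses), so the affected measures are ones the study will be judged on. The Reference standard rule also drops the whole patient for want of a definitive diagnosis, even where the experts could agree on the subspecialty, so usable triage data are lost.

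**Working it through.** **Timing.** The 3-month rule is late by construction. For rare diseases the timing is inferred. In the early clinical stage, data collection precedes the physician's diagnosis, and in both stages the data-entry staff do not know the reference standard and so cannot screen on it. A patient who attends with an already known rare diagnosis could still be screened out earlier. In the silent stage the researchers observe the consultation, so the inference is weaker there.

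**Inputs.** The document gives no figure for the share excluded or for AI performance in those patients, so there is no plan figure to reproduce. Assumed: 100 patients, of whom 5 have a rare disease; equally common labels; errors spread evenly; all 5 rare patients given one of the common labels.

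**Sensitivity.** Each retained disease's sensitivity is TP/(TP+FN) among patients with that disease. Adding rare-disease patients changes neither term.

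**Specificity, four labels, 95.0% among retained patients.**
- Per label: 95/4 = 23.75 patients with the disease and 71.25 in the rest group; false positives 0.05 × 71.25 = 3.56.
- Add back: 5/4 = 1.25 further false positives; rest group 71.25 + 5 = 76.25.
- Specificity = 1 − (3.56 + 1.25)/76.25 = 93.7%, a fall of about 1.3 points to below the 95% target.

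**Specificity, twenty labels, 75% of retained patients correct.**
- Per label: 95/20 = 4.75 with the disease and 90.25 in the rest group; errors 0.25 × 95 = 23.75, or 1.19 per label; specificity 1 − 1.19/90.25 = 98.7%.
- Add back: 5/20 = 0.25 false positives; specificity = 1 − (1.19 + 0.25)/95.25 = 98.5%, a fall of about 0.2 points, still above target.

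**When specificity is not overstated.** It falls only if rare patients receive a given label more often than the retained rest group does. With four labels that rate is 5%, so the break-even is 4 × 5% = 20% of rare patients mislabelled.

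**PPV for diagnosis.** A mislabelled rare patient adds a false positive and no true positive, so PPV can stay the same or fall but cannot rise.
- Four labels: TP = 23.75 − 3.56 = 20.19. PPV goes from 20.19/23.75 = 85.0% to 20.19/25 = 80.8%.
- Twenty labels: TP = 4.75 − 1.19 = 3.56. PPV goes from 3.56/4.75 = 75.0% to 3.56/5 = 71.3%.

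Unlike the specificity loss, this loss does not shrink as labels are added.

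**Patient-level accuracy.** With retained accuracy S, excluded share f and AI correctness q in those excluded, all-patient accuracy is S(1 − f) + qf.
- S = 0.75, f = 0.05, q = 0: 0.75 × 0.95 = 71.3%.
- S = 0.75, f = 0.05, q = 0.25: 0.7125 + 0.0125 = 72.5%.
- q = S: no change.

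**Unresolved diagnoses.** With an unresolved share u, accuracy lies between S(1 − u) and S(1 − u) + u. For S = 0.75 and u = 0.10 (assumed), that is 0.675 to 0.775. The interval contains 75%, so the direction is undetermined.

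**The case against.** The strongest reply is that the scope is declared: the Discussion limits the evaluation to common diseases, the Limitation section asks for further evidence on rare ones, and the registration-desk use is a statement of potential. This stands in part. It justifies giving no separate sensitivity for rare diseases. It does not justify removing those patients from the rest group, and the stated limitation names a different cause.

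It can also be said that the assumption of total mislabelling is a worst case. That is right. The text component is a ChatGPT prompt with no stated closed list of labels, the Outcome measure rules allow partial matches to be discussed, and a rare disease may still be triaged to the correct subspecialty. In silico development plans ten subspecialties with one to five diseases each, so four labels is an unfavourable case for specificity. Patients without a reference diagnosis cannot be scored for diagnosis at all, so some loss there is unavoidable.

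A reader might infer more than the text supports:
- That eligibility is set by the study's own results. The threshold's source is not stated. The only disease-frequency source named in Eligibility criteria is the Shanghai hospital's outpatient data for the preceding 3 years, from which it could be fixed beforehand.
- That the threshold means 5% prevalence and would remove most diseases. The printed wording is a percentile, which may affect very few patients.
- That the 75% and 85% targets are themselves at risk. In Hypotheses these are sensitivity targets for diagnosis, and sensitivity for retained diseases does not change.

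**Conclusion.** The point holds as a defect in how the analysed population is fixed. One exclusion is explicitly made after the AI data are entered, the other mostly is by inference, and nothing in the article brings these patients back. Removing rare-disease patients can overstate specificity, PPV and overall accuracy for undiagnosed attenders. The size cannot be derived from the document. At an assumed 5% rare share with every such patient mislabelled, the loss is about 0.2 to 1.3 points of specificity, depending on the number of labels, and 3.7 to 3.8 points of patient-level accuracy from a 75% level (2.5 points if a quarter are labelled correctly). It is nil for accuracy if the AI does as well in rare disease as elsewhere. It would be wrong to call the whole effect one-directional, because for unresolved patients the bounds run both ways. The undefined threshold is a fault in its own right, since it leaves the number of patients removed open.

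**What to change.** 1. Delete the rare-disease exclusion, or limit it to not reporting a separate sensitivity for those diseases. If a threshold is kept for that purpose, fix its definition and source population in advance.
2. Keep these patients in the rest group of every one-vs.-rest table and in overall accuracy, scored by the existing Outcome measure rules. Do not add an exception for out-of-scope answers, because those rules count a failure to provide any diagnostic information as incorrect.
3. Keep patients without a definitive diagnosis in the triage analysis when at least three of five experts agree on the subspecialty.
4. For diagnosis, report the number of such patients and show best-case and worst-case accuracy.
5. Retain the exclusion-based figures as a secondary analysis, and name the exclusion in the Limitation section.

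The cost is revised eligibility wording, a little more analysis of patients largely already consented and reviewed, and probably somewhat less favourable headline figures.
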